## Outcome measures

### Primary outcome measure

Response to treatment will be measured using a surrogate endpoint. It is not feasible to use ‘malignant transformation’ as an endpoint in this context, as a large, long-term study would be required to allow sufficient time for enough events to occur for statistical power. The primary endpoint itself will be derived as a composite score of changes in lesion size, changes in histological grade and loss of heterozygosity (LOH), which is advised in the context of rare events.

#### Assessment of lesion size

Lesion size will be calculated based on the estimated elliptical area given by the longest length of the lesion and the associated perpendicular width. Lesion size response will be then measured on a 7-point scale ranging from − 3 to 3 based on the change in lesion size between pre and post-treatment assessment (Table 3).

**Table 3 Tab3:** Scale for measuring change in the size of clinical lesion

Change in lesion size	Code
≥ 75% decrease	3
50–74 % decrease	2
25–49% decrease	1
0–24% decrease or increase	0
25–49% increase	− 1
50–74% increase	− 2
≥ 75% increase	− 3

#### Assessment of histology response score

A 9-point scale will be used to obtain the histological score as related to the grade of dysplasia. The histology response score is the original pathology score minus the final pathology score (from the specimen obtained at the end of the 4-month treatment period). See Table 4.

**Table 4 Tab4:** Histological scoring scale

Score	Histological diagnosis
0	Normal with or without hyperkeratosis
1	Atypia with crisply defined clinical margins
2	Mild dysplasia
3	Mild-moderate dysplasia
4	Moderate dysplasia
5	Moderate-severe dysplasia
6	Severe dysplasia
7	Carcinoma in situ
8	Invasive squamous cell carcinoma

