## Methods and analysis

### Study design and objectives

The SAVER trial is a phase IIb multicentre, open-label, randomised control trial of VPA vs observation only in patients with high-risk OED (see Table 1). The aim of this trial is to investigate the effects of VPA as an epigenetic chemopreventive therapy in high-risk OED. The primary objective is to determine: clinical activity of sodium valproate in high-risk OED, using a composite surrogate endpoint of change in the size of clinical lesion, changes in loss of heterozygosity profile and change in grade of dysplasia (see the ‘Outcome measures’ section). The key secondary objectives are to determine, in subjects with high-risk OED: the mechanism of action of VPA, associated toxicity, overall survival, development of any cancer and the feasibility of conducting such research in the UK National Health Service.

**Table 1 Tab1:** Definition of a high-risk lesion

Definition of a high-risk lesion:	
The index lesion is deemed at high risk of malignant transformation (i.e. estimated >20% over 5 years) if:	
a. Diagnosed as severe OED (WHO grade) or;	
b. Diagnosed as mild or moderate OED (WHO grade), with at least one additional high-risk feature(s) from the list below:	
i. Patient is a non-smoker (less than 100 cigarettes or equivalent over whole lifetime)	
ii. Lesion size > 200 mm^2^	
iii. Lateral tongue site	
iv. Mucosal speckling or heterogeneous appearance	
v. Patient had an excised OSCC during previous 5 years (but not within previous 6 months).	

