### Study population and inclusion criteria

Patients will be recruited via Oral Medicine, Oral and Maxillofacial Surgery outpatient and Oral Dysplasia Multidisciplinary clinics at the study sites. Eligible patients will have a lesion that is accessible, measurable (at least 100 mm^2^), amenable to clinical photography and located in the oral cavity or oropharynx or on the lip. As part of the screening process for SAVER, all patients will require an incisional biopsy of the index lesion to confirm eligibility; only patients with a biopsy confirming a histopathological diagnosis of OED, considered to be at high risk of transforming to oral cancer, will be included. The definition of a high-risk lesion can be found in Table 1.

There must be a treatment plan for either surgical resection or close monitoring (clinical and photographic follow-up). The patient must be fully informed, have received Patient Information Sheet (PIS) and considered this during a ‘cooling-off’ period, be competent to consent, age ≥ 18 and able to comply with minimum attendance requirements. Exclusion criteria can be found in Table 2.

**Table 2 Tab2:** Exclusion criteria for the SAVER trial

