**Exclusion criteria**	
1. Synchronous or metachronous OSCC (i.e. at time of screening or within 6 months)	
2. Active malignancy outside head and neck region (with exception of non-melanoma skin cancer)	
3. Currently positive for COVID-19 (patients who have recovered from COVID-19 are NOT excluded)	
4. OSCC susceptible conditions e.g. Fanconi anaemia, Blooms syndrome, ataxia-telangectasia and Li-Fraumeni syndrome	
5. Clinical and/or histopathological diagnosis of oral submucous fibrosis	
6. Immunosuppression. However, low dose i.e. < 10mg/day prednisolone, or equivalent steroid, (as per BNF conversion table), are not considered an exclusion.	
7. Chronic previous or current use of sodium valproate	
8. Diagnosed epilepsy that has chronic previous or current use of *any* antiepileptic therapy	
9. Obesity (body mass index ≥ 30)	
10. Known relative or absolute contraindications to Sodium Valproate (as listed in British National Formulary), and specifically:	
a. Acute porphyria	
b. Known or suspected mitochondrial disorders	
c. Personal or family history of severe hepatic dysfunction, current hepatic dysfunction (as evidenced by LFTs outwith reference range and prolonged prothrombin time)	
d. Past history or current pancreatitis	
e. Women with child-bearing potential. A woman is considered of childbearing potential (WOCBP), i.e. fertile, following menarche and until becoming post-menopausal unless permanently sterile. Permanent sterilisation methods include hysterectomy, bilateral salpingectomy, and bilateral oophorectomy.	
f. Potential drug interactions (particularly antipsychotic and anticonvulsant medications, MAO inhibitors, antidepressants, benzodiazepines), specifically patients taking phenobarbital, primodone, carbopenem antibiotics (imipenem, panipenem, meropenem), cimetidine, erythromycin, lamotrigine, olanzapine, pivmecillinam, sodium oxybate, zidovudine, carbamazepine, phenytoin, rifampicin, high dose salicylates including aspirin > 75 mg daily (patients taking low dose aspirin 75 mg daily are eligible).	
g. Patients with suicidal ideation and behaviour should be excluded from the trial. Patients should also be monitored for signs of suicidal ideation and behaviours and appropriate treatment should be considered.	
h. Patients with known or suspected mitochondrial disease, systemic lupus erythematosus or hyperammonaemia	

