#### Arm B

Patients in the control group will not receive any trial medication. They will be monitored at the same intervals as patients in Arm A (2, 4 and 6 months from baseline) and will subject to the same blood monitoring schedule. A 5-mm punch biopsy will be taken at the 4-month time point, as for Arm A.

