### Schedule of events

Figure 1 shows the flow of patients through the trial and the SPIRIT figure (Fig. 2) gives details of the procedures required at each trial time-point. A screening biopsy (incisional biopsy) is taken to confirm eligibility, prior to randomisation. Patients are randomised to one of two arms (sodium valproate or observation only), for 4 months. A repeat biopsy is taken on the final day of trial medication at the 4-month time-point for both groups. A clinical photograph and bloods are also taken at this visit for both groups. In total the patient is examined five times during the trial period for signs of lesion progression.

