### Blinding

SAVER is an open-label trial. The primary endpoint of the trial consists of objective assessments of lesion size using a clinical photograph, grade of dysplasia and loss of heterozygosity studies. These will all be assessed by blinded assessors.

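### If the entry biopsy read is reused as the baseline histology score, both arms drift slightly toward response; a masked paired re-read removes the drift

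*Protocol article*

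**What the plan says.** All references are to the protocol article.

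- **Score.** Under Assessment of histology response score, the component is a difference on a 9-point scale (0 to 8): "The histology response score is the original pathology score minus the final pathology score". The final specimen is the one taken at the end of the 4 months.
- **Baseline specimen.** Study population and inclusion criteria states that "all patients will require an incisional biopsy of the index lesion to confirm eligibility". Schedule of events places it before allocation: "A screening biopsy (incisional biopsy) is taken to confirm eligibility, prior to randomisation".
- **Entry depends on its result.** "only patients with a biopsy confirming a histopathological diagnosis of OED, considered to be at high risk of transforming to oral cancer, will be included". In Table 1, severe dysplasia qualifies alone. The other route is "Diagnosed as mild or moderate OED (WHO grade), with at least one additional high-risk feature(s) from the list below". At the top of the scale, Table 2 excludes "Synchronous or metachronous OSCC (i.e. at time of screening or within 6 months").
- **Final specimen.** It is a 5-mm punch in both arms. For the control arm: "A 5-mm punch biopsy will be taken at the 4-month time point, as for Arm A".
- **Threshold.** Under Total responsiveness score, a total of 1 or more is a response. A fall of one histology step is therefore enough when the size and LOH components are 0.
- **Blinding.** Of size, grade and LOH: "These will all be assessed by blinded assessors". Masking to time point and paired reading are not mentioned.

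**The concern.** A measurement used to select patients is a poor baseline for measuring change. A lesion read one step too high is more likely to be admitted, and one read too low is more likely to be left out. Among those admitted, the average baseline error is then positive. The month-4 read passes no such filter, so its error averages zero, and the difference drifts toward response with no biological change.

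The endpoint turns a one-step difference into a responder, so even a small drift moves some patients across the line. Two things are at stake: the absolute response rates, which are meant to inform a phase III trial, and some dilution of the contrast that the trial is powered to see.

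**Working it through.** **1. The plan's own figure.** Inputs from Sample size calculation and Statistical analysis: 33 control and 67 treated patients, response 20% v 40%, one-sided 0.16, stated power 82%. Exact enumeration with a one-sided Fisher test gives 0.805. A rule on the difference in proportions, with size held to at most 0.159 at any common rate, gives 0.841. The stated 82% lies between the two, so the design reproduces.

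**2. Mechanism.** Let the true grade be T, the entry read T + e1 and the final read T + e2, with no true change. The score is (T + e1) - (T + e2) = e1 - e2. Since e2 is not selected on, its mean is 0, and the drift is the mean of e1 among those admitted. The lower cut-off and the easier route for severe grades make this positive. Excluding carcinoma at the top pulls the other way. An independent baseline re-read replaces e1 by an unselected error, and the drift becomes 0.

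**3. Histology alone.** The article gives no reading-error figures, so all inputs here are assumptions.

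*Model A:* errors of one step, 50-70% exact agreement of a read with the true grade, 30-70% of patients with a risk feature.

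| Baseline used | Mean drift | Score of 1 or more |
|---|---|---|
| Entry read | +0.07 to +0.18 | 26-38% |
| Independent re-read | 0 | 23-32% |

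The excess due to selection is 26 - 23 = 3 points at the low end and 38 - 32 = 6 at the high end. The remaining 23-32% is ordinary reading error.

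*Model B:* normal latent grade with SD 1.5, the severe route included, 60% of the others with a risk feature. At reading SD 0.5, two reads agree exactly in 1 - 0.257 - 0.257 = 49%.

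| Mean latent grade | Entry read | Re-read | Excess |
|---|---|---|---|
| 3 | 28.8% | 25.7% | 3.1 points |
| 4 | 27.5% | 25.7% | 1.8 points |
| 5 | 26.3% | 25.7% | 0.6 points |

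Much noisier reading enlarges the excess. With mean grade 2 and reading SD 1.5 it is 55.3 - 39.6 = 15.7 points, but two reads then agree exactly in only 1 - 0.396 - 0.396 = 21%. If the severe route is ignored and the source population averages grade 5, the drift reverses slightly (-0.02 to -0.09).

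**4. Composite.** Model A was rerun with four assumed grade mixes, 50% or 70% agreement, 30% or 70% with a risk feature, and size and LOH each scoring -1 or +1 by chance (10% or 25% each way). This makes 32 input sets. The excess response on the total score is about 1 to 5 points, the same in each arm.

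**5. Power.** Suppose artefact adds 5 points to control, from 20% to 25%.

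- If the 20-point gap is kept (25% v 45%), Fisher power is 0.790, a loss of 1.5 points.
- If artefact purely dilutes, a fraction a of non-responders is misclassified. Then 0.20 + 0.80a = 0.25 gives a = 0.0625, and treatment becomes 0.40 + 0.60 × 0.0625 = 0.4375. Power is 0.752, a loss of 5.3 points.
- For a 1-point excess the same two rules give 0.801 and 0.794, losses of 0.4 and 1.1 points.

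In the 32 sets, starting from the higher rates that reading error already produces and with full dilution, 24 lose less than 4 points. The largest loss is about 6.

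**6. Specimen type.** A 5-mm punch covers 3.14 × 2.5² = 19.6 mm². The article gives neither size nor technique for the incisional biopsy, so no ratio can be formed. With the entry read and model B's range of inputs, an assumed half-grade under-call by the punch gives a score of 1 or more in 48-64%. A half-grade over-call gives 9-44%. The assumption fixes the direction; the document does not.

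**The case against.** The strongest reply is that the article never says the entry read is the scored read. Eligibility uses WHO grades and the endpoint a separate 9-point scale. Grading is said to be blinded, and under Confidentiality tissue reaches the pathology laboratory under the randomisation number, which exists only after allocation. A separate coded read of the baseline slide is therefore possible. This stands: the point is conditional, and one sentence confirming a re-read would close it. It does not remove the point, because the wording most naturally means the report already in hand, and blinding to arm cures nothing in a read made before randomisation.

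It can also be said that slide-reading detail belongs in the full protocol. That holds for laboratory procedure, but which read enters the subtraction is part of the endpoint definition.

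A reader might infer four stronger things that the document does not support:

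- **Bias for valproate.** Both arms have the same biopsies at the same times and blinded grading, so the null comparison is fair.
- **Selection alone lifts control above the planned 20%.** The 26-38% is histology only and mostly ordinary reading error. The 20% refers to the composite, where other components can cancel a histology point, and its derivation is not given.
- **The change from incisional to punch biopsy favours response.** A punch can be a form of incisional biopsy, the month-4 sample is called a repeat biopsy, and samples from both times are bisected.
- **The reader knows which slide is the final one.** Nothing says so.

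**Conclusion.** The concern holds in a limited, conditional form. If the entry read is the original score, regression to the mean moves both arms toward response. With assumed grade mixes and 50-70% exact agreement, the absolute rate in each arm is overstated by roughly 1 to 5 points. Power changes by about 0 to 4 points on most inputs, and by 5 to 6 if every artefactual response is pure dilution at the top of that range. Type I error is unaffected. The larger source of false responders, reading error at a one-step threshold, is separate and would survive a re-read. An effect of specimen type is possible, but its size and direction cannot be established. This is a cheap improvement to a component of the primary endpoint and does not undermine the trial.

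**What to change.** In Assessment of histology response score and in Blinding, state that the screening read determines eligibility only. Take the endpoint score from a single batch read by the existing central pathology unit. Each patient's stored baseline and month-4 slides should be graded on the 9-point scale by the same reader, in random order, masked to arm and to time point. If this is already done, say so.

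The cost is re-reading about 110 stored baseline slides. No extra biopsy or additional reader is needed, and patients already enrolled can be included from stored slides. The screening biopsy technique should be left as it is: it serves diagnosis, and the document gives no basis for changing it on these grounds. The re-read removes the drift but not ordinary reading error.

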#### Assessment of loss of heterozygosity (LOH) response score

LOH has been identified as a prognostic marker for progression of OED, with lesions displaying LOH at 3p and 9p having a 22-fold increased risk of progression to OSCC [20]. The following 8 loci and associated genes have been selected based on previous evidence of their predictive value in the progression of OED:
3p14 [D3S1007 (VHL), D3S1234 (FHIT)]9p21 [D9S171, D9S1748 (P16/CDKN2A), D9S1751 (P16)]9p22 (IFN-a)17p13 [D17S786 (P53) and TP53]

For each loci, a score of +1 is given if it is positive for LOH and zero if it is negative for LOH. The LOH response score will be the pre-treatment score minus the post-treatment score.

#### Total responsiveness score

The total responsiveness score for each patient will be calculated as follows: lesion size response score + histological response score + LOH response score. Patients will be classified as ‘disease progression’ with a response score ≤ − 1, ‘stable disease’ with a response score between − 1 and 1 and ‘response to treatment’ with a response score ≥ 1. The only exception to these criteria is for patients with confirmed malignant transformation. These patients shall automatically be categorised as having disease progression, irrespective of their responsiveness score. The disease response rate will compare patients with response to treatment against patients with either stable disease or disease progression.

### Secondary outcome measure

Secondary endpoints will be assessed including toxicity (measured using Common Terminology Criteria for Adverse Events (CTCAE) v4.03 classification), overall survival and malignancy of the head and neck (or other sites) during the patient’s active trial period and for the total duration of the trial. Feasibility endpoints will be recorded, defined by overall and centre-specific rate of recruitment, compliance with treatment, protocol deviations and drop-out rates.

### Mechanistic sub-study

VPA has a known mechanism of action as a histone deacetylase inhibitor (HDACi). The reduced risk of head and neck cancers demonstrated in patients taking VPA has been hypothesised to be through epigenetic reprogramming of oral potentially malignant disorders [12]. As part of an embedded mechanistic sub-study, we will assess tissue-specific epigenetic changes, changes in gene expression, expressed markers of proliferation, apoptosis and senescence. We will also assess pharmacodynamic biomarkers of histone acetylation in circulating white cell DNA, from venous blood samples taken at the 2- and 4-month time points. The presence of a control group will enable us to determine whether these effects are specific to VPA. Tissues samples will be obtained before and after drug treatment. Samples will be bisected and half used for histology and immunohistochemistry and half used for RNA/DNA preparation.

### Qualitative sub-study: the SAVER information study

This is the first UK-based chemoprevention trial in OED, therefore we will explore patients’ perspectives on the acceptability of SAVER and their experience of recruitment and participation in the trial. This will be achieved through 20 qualitative interviews, or until data saturation is reached. The aim is to improve patient information resources and to enhance the design and acceptability of a future phase III trial. We will interview patients who declined to participate in the trial and those who took part; we will aim for diversity in key characteristics: demographics, trial site and proposed treatment (surgery vs surveillance).

### Sample size calculation

Sample size calculations are carried out on the principles of a single-stage Jung design for randomised phase II studies based on exact binomial probabilities and allowing for unequal allocation [21]. The primary outcome is the response rate; a rate of 20% is estimated for the control arm with a 20% rate increase in the treatment arm representing the minimal clinically important difference. With a type I error of 0.16 and 82% of power, 100 patients (33 in the observation-only arm and 67 in the treatment arm) will be required in the study. Adjusting for a potential 10% drop-out rate, the final sample size will be of 110 patients (37 in the observation-only arm and 73 in the treatment arm).

The intent of the study will be to recruit the 110 patients required over a period of 32 months, assuming 10 sites recruiting at an average rate of 0.4 patients per site per month.

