### Randomisation

Randomisation will be completed centrally by the LCTC via a password-protected web-based tool called the Treatment Allocation Randomisation System (TARDIS). All patients will be allocated a unique randomisation number. Randomisation must be carried out within 90 days of the research biopsy report and commencement of trial treatment within 30 days of the date of randomisation. Patients will be randomised between VPA (arm A) and observation only (arm B) in the ratio 2:1, with site used as a stratification factor.

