### Statistical analysis

There will be no formal stopping rules or interim analysis based on patients’ response rate. However, an Independent Safety and Data Monitoring Committee (ISDMC) will meet at regular intervals to review and assess the conduct of the study and the accumulated data. The ISDMC will be able to make appropriate recommendations to the Trial Steering Committee (TSC) on grounds of toxicity and feasibility.

The study will be analysed and reported in line with the Consolidated Standards of Reporting Trials (CONSORT). Statistical analyses will be carried out following the intention to treat principle (ITT), with the exception of toxicity which will be analysed on the basis of the actual treatment received. Missing data are not anticipated to be substantial in the study and therefore the final analysis shall be performed on a complete case basis. However, if more than 10% missing data are observed on the primary outcome, multiple imputation technique by chained equations shall be used.

Continuous variables will be summarised as median and interquartile range and categorical variables will be presented as frequencies of counts with associated percentages. Primary analysis on the primary outcome will be performed using a stratified Mantel Haenszel test and results will be assessed with a one-sided p value of 0.16 as the threshold for statistical significance. The primary efficacy parameter (odds ratio) will also be reported with the one-sided 84% confidence interval. Logistic regression will be used to investigate the relationship of the primary outcome with key prognostic covariates. Analyses of categorical secondary outcome will mirror that of response rate, using stratified Mantel Haenszel test and logistic regression techniques. Time to event data will be compared between arms by stratified log-rank test. Further analyses on survival data shall be carried out using Cox models if, after inspection of Schoenfeld residuals, the proportional hazard assumption is not violated. All secondary analyses will be assessed by the nominal two-sided p value of 0.05 to determine statistical significance.

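### The 110-patient target absorbs 9.1% drop-out rather than the stated 10%: at 10% loss, 99 patients remain instead of 100, with negligible effect on power

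*Protocol article*

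**What the plan says.** The Sample size calculation section of the protocol article uses a "single-stage Jung design for randomised phase II studies based on exact binomial probabilities and allowing for unequal allocation". The planning rates are given as "a rate of 20% is estimated for the control arm with a 20% rate increase in the treatment arm", which is read here as 20% against 40%. The requirement before drop-out is "100 patients (33 in the observation-only arm and 67 in the treatment arm) will be required", at a type I error of 0.16 and 82% power. The next sentence reads "Adjusting for a potential 10% drop-out rate, the final sample size will be of 110 patients", with the arms given as "37 in the observation-only arm and 73 in the treatment arm".

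Three statements elsewhere bear on the point. The Randomisation section allocates "in the ratio 2:1, with site used as a stratification factor". The Statistical analysis section makes the primary test one-sided: "results will be assessed with a one-sided p value of 0.16 as the threshold for statistical significance". That section also plans a complete-case final analysis and turns to multiple imputation only if more than 10% of primary outcomes are missing.

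The article does not state the formula used for the drop-out adjustment.

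**The concern.** A drop-out rate applies to the patients recruited. To keep a required number n after losing a fraction d, n/(1 − d) must be recruited. Recruiting n × (1 + d) falls slightly short, because the loss is then taken from the larger number.

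The two sentences of the sample size section therefore do not fit together: at the loss the plan assumes, the number it calls required is not reached. The missing-data rule makes this concrete. If drop-out means a missing primary outcome, exactly 10% loss is 11 of 110. That does not exceed the 10% trigger for imputation, so the primary analysis would run on 99 complete cases.

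What is at stake is the internal consistency of a printed calculation, and whether the shortfall is large enough to affect the stated power.

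**Working it through.** **Inputs.** From the Sample size calculation section: required n = 100 (67 treatment, 33 observation); drop-out d = 10%; final N = 110 (73 and 37); response rates 20% and 40%; type I error 0.16; power 82%. From the Randomisation section: 2:1 allocation. From the Statistical analysis section: one-sided test.

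**Step 1: reproduce the plan's figure.** 100 × 1.10 = 110. Split 2:1, 110 × 2/3 = 73.3 and 110 × 1/3 = 36.7, which round to 73 and 37. This matches the printed figures exactly. That multiplication by 1.1 was used is inferred from this match.

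**Step 2: apply the stated loss to the stated target.**
- Total: 110 × 0.9 = 99, against 100 required.
- Treatment: 73 × 0.9 = 65.7, against 67.
- Observation: 37 × 0.9 = 33.3, against 33.

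The expected split is about 66:33.

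**Step 3: find the loss that 110 does absorb.** (110 − 100)/110 = 9.1%.

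**Step 4: inflate by n/(1 − d).**
- Total: 100/0.9 = 111.1.
- Treatment: 67/0.9 = 74.4, rounded up to 75.
- Observation: 33/0.9 = 36.7, rounded up to 37.
- Sum by arm: 112.

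This is two more recruits than stated. With equal proportional loss in the arms, both belong to the treatment arm.

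**Step 5: effect on power.** Power was found by enumerating all pairs of binomial outcomes for 20% against 40% at one-sided 0.16.

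| Test | 67:33 (n = 100) | 66:33 (n = 99) |
|---|---|---|
| Unconditional exact test on the rate difference, type I error controlled over all common rates | 84.1% | 82.6% |
| Exact test on the rate difference, type I error controlled at a common rate of 20% only | 87.7% | 86.4% |
| Mantel-Haenszel, unstratified | 86.0% | 86.4% |
| Fisher exact | 80.5% | 79.8% |

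Both versions of the exact binomial test stay above 82% at 66:33. The Mantel-Haenszel figure rises slightly with one patient fewer, because power moves in steps when the outcomes are counts. Fisher's test is below 82% at the full 67:33, so the drop-out allowance is not what puts it there. The article does not give the exact form of the rejection rule, so these rows show a range and are not a reproduction of the stated 82%.

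**The case against.** The strongest objection is that the point is immaterial. The article calls the 10% drop-out only potential, and the difference between 9.1% and 10% is well inside the uncertainty of such a planning guess. Chance imbalance under 2:1 randomisation stratified by up to 10 sites, or uneven loss between arms, could shift the analysed split by more than one patient. All of this stands. It limits the weight of the point, but it does not make 110 × 0.9 equal 100.

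It can also be said that the formula is inferred. That is correct, but the mismatch does not depend on it: whatever formula was used, 10% loss from 110 leaves 99.

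Two stronger readings are tempting, and the document supports neither.

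- **That the trial misses its stated power.** A reader might point to Fisher power falling from 80.5% to 79.8%. Fisher's test does not reach 82% even with all 100 patients, and 80% is not a threshold in this plan. Under the unconditional exact binomial test, 99 patients still give about 82.6%.
- **That the recruitment targets are wrong as a result.** The Recruitment section sets milestones of 43 and 88 patients at 12 and 24 months beside an assumed rate of 0.4 patients per site per month over ten sites. Nothing there derives them from the drop-out allowance. The assumed rate over 32 months gives 10 × 0.4 × 32 = 128, above both 110 and 112.

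**Conclusion.** The arithmetic mismatch holds and can be checked from the sample size section alone. The stated target falls one evaluable patient short of the stated requirement at the stated loss, equivalent to two recruits, and it absorbs 9.1% loss instead of 10%.

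The consequence is negligible. Across the tests above, the change in power between 67:33 and 66:33 runs from a loss of 1.5 percentage points to a gain of 0.4, and the stated 82% is not shown to be lost.

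This rests on three assumptions: the 20% increase is absolute; drop-out means a missing primary outcome; and loss is proportionally equal in the two arms. The Mantel-Haenszel figures ignore the stratification by site. This is a minor correction of wording, and neither the design nor the analysis needs to change.

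**What to change.** Reword the drop-out sentence in the Sample size calculation section. Keep 110 (73 and 37) and state either that it allows for about 9% drop-out, or that 10% drop-out would leave 99 evaluable patients (about 66:33). In the second case, give the power for that size under the stated exact design, and name the rejection rule used so that the figure can be reproduced.

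The cost is one sentence. No additional patients are needed, and the 110 quoted in the Abstract and the Recruitment section can stay. Printing 112 (75 and 37) would also make the arithmetic agree, but the power results give no reason to enrol two more patients.
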